# Study Endpoints

- 1. Primary endpoints for feasibility include using a 5-question Likert-style scale survey of patient reported experience and documented frequency and duration of BWSS use. Primary endpoints for utility are assessments of gross motor function and include The World Health Organization’s gross motor developmental milestones, Bayley Scales of Infant Development v.3 Gross Motor subtests, Hammersmith Functional Motor Scale Expanded and/or Revised, and Neuromuscular Gross Motor Outcome.

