Families will be given the option to complete the midpoint functional assessments during an in-home visit or during a regularly scheduled clinic or research appointment at NCH. Midpoint assessment visits may also occur remotely using approved video conferencing services. Photos and videos of the child performing motor skills will be accepted to incorporate into the midpoint assessment up to one week after the date of visit. Photo and video submissions will only be accepted for assessments performed remotely.

**Final Visit**: A study team member will complete final functional outcome assessments. Families will be given the option to complete the final functional assessments during the in-home visit or during a regularly scheduled clinic or research appointment at NCH. Final assessment visits may also occur remotely using approved video conferencing services. Photos and videos of the child performing motor skills will be accepted to incorporate into the final assessment up to one week after the date of visit. Photo and video submissions will only be accepted for assessments performed remotely.

Families will be provided with an opportunity to enter the Optional Enrollment Extension phase (see 6.2.1 point below).

If the family would like to continue enrollment but the BWSS is already assigned to another subject on the waitlist, the Final Visit will be completed as detailed in 9.2.1 and the family will be placed on the waitlist for re-enrollment.

6.2.1 **Final Visit - Optional Enrollment Extension:** Should the family choose to continue enrollment following the 6-month finial visit, the BWSS will remain in the family’s home until the family withdraws from the study or until BWSS equipment is needed for use with another subject.

Families will be asked to continue documenting BWSS use in Daily Activity Logs. Functional assessments may be performed, either in the home or during a regularly scheduled clinic or research appointment at every 6-9 months.

6.2.2 **Final Visit without Enrollment Extension:** A study team member will return to the family’s home to dismantle the BWSS unit. Prior to disassembly, a final equipment check using the BWSS safety Inspection Check List will be completed, reviewed, and signed by the study team member and responsible parent. Daily activity log will be checked and completion will be documented

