- 1. All functional outcome assessments will be video recorded. Parents may also submit video evidence of motor skill attainment within 7 days of any remote study visit, should the child not perform on the date of the assessment due to child’s mood or behavior.
     - Parents will submit video evidence through secured email communication. Submitted videos will be stored on secured NCH research drive, alongside other assessment videos.
  2. FFamilies will be educated on appropriate activities to help engage with their child in the harness.

Each family will receive an Activity Ideas booklet to reference throughout the duration of the study (Appendix F).

- 1. Families will be asked to fill out the Daily Activity Log (Appendix G) each time the harness is used. The log will include information on the duration and frequency of BWSS use, activities completed with child while in BWSS, and any observed changes in child’s motor function
  2. Families may be asked to attach a motion sensor to the harness system.
  3. **Liability Waiver and Legal Agreement**: Families are to review and sign a liability waiver prior to in-home equipment set-up. This documentation to be created by Nationwide Children’s Hospital Corporate Legal Services department and addresses the expectations and responsibilities of the families to maintain the integrity of the BWSS for the duration of the study
  4. **Safety Considerations**
     - **Equipment Inspection**
       - Equipment will be required to pass study team member inspection using the BWSS Inspection Checklist provided by Enliten, LLC. (Appendix A)
       - Equipment safety checks will occur at screening (prior to in-home set up), baseline, and final visit. Photographs or video of in-home set up will be included in safety documentation.
       - It will be required that the BWSS Inspection Check List be completed by the study team member and reviewed and signed-off by the study team member and parent at baseline and final study visit.
     - **Adult Supervision**
       - Families are required to supervise their child while using the BWSS at all times.
     - **Family Training**

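### The protocol gives two different rules for which family-submitted evidence counts toward a remote motor assessment, so a primary utility score can depend on which rule is followed

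*Protocol*

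**What the plan says.** All the relevant text on submissions is in the Protocol, Procedures Involved.

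- **Midpoint Assessment Visit:** "Photos and videos of the child performing motor skills will be accepted to incorporate into the midpoint assessment up to one week after" the visit date.
- **Final Visit:** "Photos and videos of the child performing motor skills will be accepted to incorporate into the final assessment", with the same one-week limit after the visit date.
- **Both paragraphs** add one limit: "Photo and video submissions will only be accepted for assessments performed remotely". Neither asks why the skill was not shown live.
- **The later item on video recording of functional assessments:** "Parents may also submit video evidence of motor skill attainment within 7 days of any remote study visit", with the condition "should the child not perform on the date of the assessment due to child’s mood or behavior". It then gives a route (secured email) and a storage place for submitted videos. It does not mention photos.

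Study Endpoints gives the scores their standing: "Primary endpoints for utility are assessments of gross motor function". Data Management and Confidentiality says that baseline and final scores will be compared.

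**The concern.** Whether an item counts as attained is part of the definition of the outcome. Here that definition is written twice, with different content. Under the visit paragraphs, a remote score can become the best performance over the visit day plus the following week. Under the later item, a submission stands in only for a performance that mood or behavior prevented on the day.

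The study has one arm and is small (15 subjects expected locally, up to 50 in the Study Summary), and its utility result is a baseline-to-final change. The visit paragraphs provide for submissions at midpoint and final. The Screening/Baseline paragraph mentions neither a remote assessment nor submissions. A generous rule at the final visit therefore adds to the change score in one direction, and there is no control group in which the same effect would appear and cancel.

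**Working it through.** The protocol states no figure on this point, so there is none to reproduce. The check is a comparison of the two texts, followed by an illustration of size.

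**1. Side by side**

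| Point | Midpoint and Final Visit paragraphs | Later item on video recording |
|---|---|---|
| Evidence | Photos and videos | Video only is named |
| Condition | None | Child did not perform because of mood or behavior |
| Window | Up to one week after the visit | Within 7 days of the visit |
| Visit mode | Remote only | Remote only |

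The texts agree on mode and, in substance, on the window. They differ on evidence and condition, which together decide admissibility.

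**2. Test cases at a remote final visit**

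- *A cooperative child tries a skill and fails, and is filmed succeeding four days later.* Admissible under the visit paragraphs. Not admissible under the later item, because its condition is not met.
- *A family sends only a still photo of the child standing, within the week.* Admissible under the visit paragraphs. The later item does not provide for it.
- *A child refuses because of mood and is filmed succeeding later in the week.* Admissible under both, even if the skill first appeared after the visit.

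The first case is a clear conflict, the second an unresolved gap, and the third no conflict.

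**3. Illustration of size**

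The protocol gives no inputs, so all of these are assumptions. Let *p* be the chance of success on any one day for an emerging item (0.2, 0.3, 0.5), *m* the chance of refusal for mood on the visit day (0.10, 0.25), and *w* the chance of at least one filmed success in the following week. Assume also that an admissible clip earns the item.

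- Success at the visit: v = (1 − m)p
- Credit under the later item: v + m·w
- Credit under the visit paragraphs: v + (1 − v)w
- Gap: w(1 − v − m) = (1 − m)(1 − p)w

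*Upper scenario: seven independent filmed attempts, w = 1 − (1 − p)^7.*

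| p | m | w | Later item | Visit paragraphs | Gap |
|---|---|---|---|---|---|
| 0.2 | 0.10 | 0.790 | 0.26 | 0.83 | 0.57 |
| 0.2 | 0.25 | 0.790 | 0.35 | 0.82 | 0.47 |
| 0.3 | 0.10 | 0.918 | 0.36 | 0.94 | 0.58 |
| 0.3 | 0.25 | 0.918 | 0.45 | 0.94 | 0.48 |
| 0.5 | 0.10 | 0.992 | 0.55 | 1.00 | 0.45 |
| 0.5 | 0.25 | 0.992 | 0.62 | 1.00 | 0.37 |

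*One further independent attempt, w = p.* The gap is (1 − m)(1 − p)p. Its lowest value is 0.75 × 0.8 × 0.2 = 0.12 and its highest is 0.90 × 0.5 × 0.5 = 0.225.

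*Ability constant over the week.* With probability *p* the child can do the item throughout, otherwise not at all. Credit under the visit paragraphs is p. Credit under the later item is (1 − m)p + m·p = p. The gap is 0.

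Per emerging item, the difference therefore runs from 0 to 0.58 over these assumptions, depending mainly on how far performance varies within a week and how often families film.

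**The case against.** The best reply is that the two texts can be read together. The later item says that parents may also submit, and it contains no word such as *only*. On this view the visit paragraphs set visit, mode and window, and the later item explains the purpose and gives the route. That reading is possible but does not fully reconcile them: if unconditional acceptance governs, the mood-or-behavior clause does nothing. The route and storage sentences also cover videos only, which leaves the accepted photos without a stated route. Nothing says which text prevails.

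Other parts of the defence stand and limit the point:

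- A reader might infer that the narrower rule never credits a skill first shown after the visit. It can, if the child refused that day because of mood or behavior.
- A reader might infer that photos are barred by the later item. They are left out, not excluded.
- Accepting a submission into an assessment is not the same as awarding the item. A study team member completes the assessment, and the instruments' scoring manuals are not part of the protocol. The conflict is over what may be considered.
- This is a single-site pilot, and remote assessment is one of three options. The protocol gives no evidence that assessors would in fact apply different rules to different children.

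**Conclusion.** The inconsistency is real and worth correcting. The protocol itself fixes the evidence rule for a primary utility endpoint, twice and differently, so this is not detail left to an analysis plan. At least one ordinary situation, an item failed at the visit and filmed successfully later, is treated in opposite ways. The wider text permits a best-of-week final score, which can raise the change from baseline without any change in ability.

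The size for this trial cannot be calculated, because the numbers of remote visits and submissions are not given. A reader might take the upper scenario (0.37 to 0.58 per emerging item, or about 1.1 to 1.7 items over three) as an estimate of bias. The document does not support that: every input is assumed, filming on all seven days with independent outcomes is a high-end case, and the gap is zero when ability is constant over the week. The conclusion rests on the wording and the test cases, not on those figures.

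**What to change.** State one admissibility rule and use it in the Midpoint paragraph, the Final Visit paragraph and the later item.

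1. **Condition.** Preferably keep the one already written: a submission counts only for items that the assessor recorded at the remote visit as not performed because of mood or behavior, and not for items attempted and failed.
2. **Evidence.** Say whether a photo may count and for which items, for example static postures only. If photos are kept, extend the submission and storage route to them.
3. **Traceability.** Add a score-sheet code for items not performed because of mood or behavior, and flag each item credited from a submission.
4. **Reporting.** Give the baseline-to-final change with and without those items.

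If the sponsor prefers the wider rule, the three places must still agree, and the final remote score should be described as best performance over the visit and the following week. The cost is a wording change and one extra code. The downside of the narrower rule is that some family-submitted material will no longer count.

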       - Families will be trained on use of the BWSS on their first home visit. Training will be conducted by an investigator on the study team and will involve: an overview of BWSS use; instructions on safely securing the child into the harness; application and technique for use of the bungee system; application and technique for use of counter-weight system; and adjusting the amount of body weight support.
       - Each family will receive an instruction manual detailing how to safely adjust the harness and amount of body weight support provided by the harness, to reference for the duration of the study (provided by Enliten, LLC; Appendix B and Appendix C).
       - Families will be instructed to leave the system as it was set-up in their home throughout the duration of the study. If the family needs to move or take down the BWSS, a safety check by a study team member will need to be completed prior to resuming use. This can be done as either an in-home visit or via a video conference call.
       - If needed, a member of the study team may call the subject’s parents to troubleshoot any technical difficulties that may arise. If the difficulties are not resolved over the phone, a member of the study team may schedule an in-home visit with the family. The family will be instructed not to use the system if they have any concerns about safety.

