# Withdrawal of Subjects*

- 1. Participation in this study is optional for the family and subject; families are given the option to withdrawal at any time. Withdrawal from this study will not affect any care provided to the patient at Nationwide Children’s Hospital. Subjects may choose to withdrawal due to lack of time/scheduling conflicts, unrelated injury of subject, outside treatments that may affect BWSS use (i.e. surgery, serical casting, etc.)
  2. Final determination of family and subject eligibility is at the discretion of the PI. If at any point during the study, the patient is determined to be un-safe while in the BWSS (e.g. change in body type or health status, un-safe practices of family noted during in-home visits) the PI may withdrawal the family from the study
  3. If subjects are withdrawn from the study, they will be instructed to discontinue use of BWSS and a clinical evaluator will come to their home to disassemble harness system and complete final safety checks.

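### The open-ended extension (6.2.1) schedules no staff inspection of the harness system while a child keeps using it, and the 50-lb limit is written only for the first 6 months

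*Protocol*

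**What the plan says.** All places are in the Protocol.

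- **Procedures Involved, Equipment Inspection.** The general rule reads: "Equipment safety checks will occur at screening (prior to in-home set up), baseline, and final visit". The checklist must be "reviewed and signed-off by the study team member and parent at baseline and final study visit". Study Timelines puts the final visit at month six.
- **6.2.2 (no extension).** The inspection is written out: "Prior to disassembly, a final equipment check using the BWSS safety Inspection Check List will be completed", and it is signed by staff and parent.
- **6.2.1 (extension).** The unit stays in the family's "home until the family withdraws from the study or until BWSS equipment is needed for use with another subject". Families go on filling in activity logs. For visits, the section says: "Functional assessments may be performed, either in the home or during a regularly scheduled clinic or research appointment at every 6-9 months". It names no equipment check.
- **Family Training.** One check is triggered by an event: "If the family needs to move or take down the BWSS, a safety check by a study team member will need to be completed" before use resumes. On how it is done: "This can be done as either an in-home visit or via a video conference call".
- **Withdrawal of Subjects, item 3.** Once use has been stopped, an evaluator goes to the home to "disassemble harness system and complete final safety checks".
- **Inclusion and Exclusion Criteria.** Body weight above 50 lb (22.68 kg) excludes a child at any time in the interventional period. Study Timelines gives that period as 6 months.

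**The concern.** The protocol writes out the inspection in the branch where use is ending and leaves it unmentioned in the branch where use goes on. After month 6 the child may still be in the harness for an unstated time, and staff have no scheduled occasion to look at the frame, springs or harness.

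Child safety is at stake. Risks to Subjects lists a fall from a wrongly fitted harness, and entanglement from misuse or equipment malfunction. Study Intervention describes spring support of up to 50 lb. A growing child can approach or pass that weight during an extension, when the written limit no longer clearly applies. No endpoint or planned comparison depends on this point, because the main comparison is baseline against the 6-month final visit.

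**Working it through.** The protocol states no inspection interval for the extension, so there is no figure to reproduce. The check sets the clauses side by side.

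**Which checks fall within continued use after month 6?**

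| Check | Trigger | Scheduled during extension use? |
| --- | --- | --- |
| Screening, baseline | Before and at set-up | No, earlier |
| Final visit with signed checklist | Month 6 | No, it comes at the start of the extension |
| 6.2.2 checklist | Before disassembly | No, use is over |
| Family Training check | Unit moved or taken down | No, event only |
| Troubleshooting home visit | Difficulty not solved by phone | No, event only |
| Withdrawal, item 3 | After use is discontinued | No, use is over |
| 6.2.1 assessments | Optional, every 6-9 months, possibly in clinic | No equipment check named |

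The number of scheduled inspections during extension use is 0.

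**Does the month-6 check lapse for extending families?** The Equipment Inspection rule has no exemption for them. 6.2.1 is itself headed as a form of the final visit, and Study Timelines fixes that visit at month six. So the rule applies. The weakness is practical: the final assessment may be remote or in clinic, and 6.2.1, unlike 6.2.2, sends nobody to the home.

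**Illustrative length of use without a scheduled check.** Inputs from Study Timelines: data collection up to 24 months, enrolment over months 0 to 12, final visit 6 months after set-up (the +2-week window is ignored). Assumptions: set-up at enrolment, the month-6 check is done, use ends with data collection, and the unit is never recalled. With enrolment at study month E, the time is 24 − E − 6:

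- E = 0: 24 − 0 − 6 = 18 months, and 18/6 = 3 times the protocol's own 6-month spacing between set-up and final check.
- E = 6: 24 − 6 − 6 = 12 months, and 12/6 = 2 times.
- E = 12: 24 − 12 − 6 = 6 months, and 6/6 = 1 time, so no excess.

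**With a repeat check, same assumptions.** Counting from set-up, for E = 0 a 6-month interval gives checks at months 12 and 18 (2 checks, longest gap 6 months). A 9-month interval gives one at month 15 (1 check, longest gap 9 months). For E = 6 there is 1 check, at month 12 or month 15. For E = 12 there is none before removal. The load is therefore 0 to 2 extra checks per extending family.

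**The case against.** The best defence is that the protocol is not silent on safety during the extension. Constant adult supervision is required. Families are told not to use the system if they have safety concerns. The investigator may withdraw a child at any point for a change in body type or health status. Families also sign a legal agreement covering their responsibility for keeping the unit in sound condition throughout the study, and an extending family is still enrolled. The manufacturer's checklist and manuals (Appendices A to C and E) are not shown and may set a maintenance interval. All of this stands, and it lowers the risk. None of it is a scheduled inspection by study staff: the measures rest on a parent or the investigator noticing a problem, and the protocol text cites no maintenance interval.

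A reader might infer three stronger points, and the documents do not support them.

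- *That 6.2.1 waives the month-6 inspection.* It does not. The general rule covers that visit, and a rule not repeated in a sub-branch is not contradicted by it.
- *That a child above 50 lb necessarily overloads the device.* Background describes unweighting part of body weight, and Study Intervention gives 50 lb as the support provided. Body weight above that figure is not automatically overload.
- *That 18 months is what the plan entails.* Units can be recalled for another subject and there is a waitlist, which would shorten extensions. The number of units is not stated.

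**Conclusion.** The point holds as an operational safety gap worth correcting. After month 6 the text permits use with no end date, schedules no staff inspection during it, and does not clearly carry the 50-lb limit forward. That much rests on the wording alone.

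The size is uncertain. The range of 6 to 18 months is illustrative. It would be shorter where a unit is recalled, and it could be longer because 6.2.1 does not tie the end of use to the end of data collection. At the lower end the gap is no longer than the spacing the protocol already accepts. The month-6 element is only a requirement not carried into the sub-section. The conclusion could soften if the unseen appendices or the family agreement set an inspection interval. It should not be read as an analysis flaw.

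**What to change.** Add to 6.2.1:

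1. The signed BWSS Inspection Check List is completed at the month-6 final visit before use continues, including when the functional assessment is remote or in clinic.
2. It is repeated at a fixed interval for as long as the unit is in use, for example every 6 months, which matches the protocol's own spacing, or at the latest at each 6-9 month contact. Because those assessments are optional, the check should be due whether or not one takes place.
3. It is done by home visit or by the video check that Family Training already allows after a unit has been moved.
4. The 50-lb limit applies for as long as the unit is used, and body weight is recorded at each contact.

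The month-6 check adds no new requirement. The rest costs one short check and one weight per contact, by existing staff. A video check cannot test fittings by hand, so it is weaker than a home visit. No document supports 6 or 9 months as a safety interval as such, so the sponsor should compare the choice with the manufacturer's material.
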